We previously reported aberrant PD-L1 expression distinct to renal compartments in ICI-related nephrotoxicity, reflecting susceptibility to develop renal irAE (20, 21). PD-L1 positivity is different in intrarenal compartments and predominantly expressed in the tubuli, which correlates with elevated serum levels of C-reactive protein (CRP) as a non-specific marker of systemic inflammation (20). Moreover, PD-L1 expression was also observed in ICI-naïve renal pathologies implying PD-L1 upregulation as an indicator of ongoing kidney damage before this becomes clinically detectable by conventional methods (20). Interestingly, urinary flow cytometry-detected PD-L1-positive (PD-L1^+^) kidney cells correlated with intrarenal PD-L1 positivity (20). Therefore, we designed a study protocol to evaluate urinary detection of PD-L1^+^ kidney cells of different origins as a tool for non-invasive and therapy-attendant biomonitoring of renal complications in cancer patients receiving immunotherapy.

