### Flow cytometry of urinary cells

Antibody staining of cells in suspension follows standard protocols. Thawed or freshly collected cells are centrifuged at 1000 rpm at 4°C for 8 minutes. The PD-L1^+^ cell line KARPAS 299 will be used as a positive control and unstained cells as negative controls for the analysis of urinary cells. Cell suspensions are washed and resuspended in PBS and stained using antibodies against PD-L1 (APC anti-human CD274, B7-H1, PD-L1, clone 29E.2A3, Biolegend, San Diego, USA) in combination with the podocyte marker podocalyxin (anti-TRA-1-81-PE, human, clone REA246, Miltenyi Biotec GmbH, Bergisch Gladbach, Germany). Identification of tubular epithelial cell (TEC) will be done by cytokeratin (anti-cytokeratin-FITC, human, clone CK3-6H5, Miltenyi Biotec GmbH, Bergisch Gladbach, Germany) with differentiation between proximal TECs by CD-10 (CD10-PE-Vio770, human, clone 97C5, Miltenyi Biotec GmbH, Bergisch Gladbach, Germany), and distal TECs by EpCAM (CD326 (EpCAM)-APC-Vio770, human, clone HEA-125, Miltenyi Biotec GmbH, Bergisch Gladbach, Germany) (22). Cells will be incubated with antibody mixtures for 15 minutes at 4°C in the dark and gated according to positive and isotype-negative controls. For dead cell identification, propidium iodide (Miltenyi Biotec GmbH, Bergisch Gladbach, Germany) will be used to gate out non-viable cells. According to standard protocols, cells will be analyzed with the FACS Canto II machine of the cell sorting unit at the Department for Hematology and Medical Oncology of the UMG.

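### As printed, the cytokeratin gate for tubular cells and the propidium iodide live gate cannot both work as intended on the same cells, so the tubular PD-L1+ readout may partly reflect membrane damage and handling

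*Protocol article*

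**What the plan says.** All the steps are in the Protocol article, *Flow cytometry of urinary cells*.

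- **Tubular marker:** "Identification of tubular epithelial cell (TEC) will be done by cytokeratin (anti-cytokeratin-FITC, human, clone CK3-6H5".
- **Subsets within the tubular cells:** "with differentiation between proximal TECs by CD-10", and "distal TECs by EpCAM".
- **Staining and gating:** "Cells will be incubated with antibody mixtures for 15 minutes at 4°C in the dark and gated according to positive and isotype-negative controls". Before this, the cells, either fresh or thawed, are spun, washed and resuspended in PBS.
- **Viability:** "For dead cell identification, propidium iodide (Miltenyi Biotec GmbH, Bergisch Gladbach, Germany) will be used to gate out non-viable cells".

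The section names no fixation step, no permeabilisation step and no fixable viability dye. It refers to standard protocols for staining and for acquisition, and cites earlier work after listing the tubular markers. The named controls are a PD-L1-positive cell line, unstained cells and isotype controls.

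On the importance of the tubular compartment, the *Introduction* says: "PD-L1 positivity is different in intrarenal compartments and predominantly expressed in the tubuli".

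**The concern.** The tubular definition needs an antibody to reach a protein inside the cell. The viability rule keeps only cells whose membrane is closed. If both apply to the same cells, the events that pass both gates are not simply viable tubular cells: they depend on how the membrane behaved during collection, freezing, thawing and staining.

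The study evaluates urinary PD-L1+ kidney cells as a marker of renal complications, and the article describes intrarenal PD-L1 as mainly tubular. A tubular count that partly tracks membrane integrity could go wrong in two ways. If leakiness varies with handling, it adds noise and weakens a true association. If leakiness varies with kidney injury itself, it could create an association that has little to do with tubular PD-L1. The documents do not show which would dominate.

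**Working it through.** No arithmetic applies, and the article gives no figure to reproduce. The check sets the printed steps side by side and follows a cell through them.

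**Inputs from the article**

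1. Tubular cells are those positive for cytokeratin; CD10 and EpCAM divide them.
2. The described staining is a 15-minute incubation at 4°C of PBS-washed cells with antibody mixtures.
3. Propidium iodide is used to exclude non-viable cells.
4. Each marker has its own fluorochrome: PD-L1 in APC, podocalyxin in PE, cytokeratin in FITC, CD10 in PE-Vio770, EpCAM in APC-Vio770. These are five different labels, which fits a single multicolour panel, although the article does not say that all share one tube.

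**Inputs from general cell biology (not stated in the article)**

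5. Cytokeratin is a cytoskeletal protein inside the cell; its antibody has little access through an intact membrane.
6. Propidium iodide enters cells whose membrane is open, whether through death or through permeabilisation.
7. CD10 and EpCAM are surface markers and can be stained on intact cells.

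**Following the steps**

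| Reading of the procedure | Cytokeratin gate | Propidium iodide gate | Result on the same cells |
|---|---|---|---|
| No permeabilisation, as printed | Stains mainly leaky cells | Discards leaky cells | The gates select against each other |
| Permeabilisation before propidium iodide | Works on all tubular cells | Dye enters all cells | Live and dead are no longer separated |
| Propidium iodide in a separate aliquot, cytokeratin tube permeabilised | Works on all tubular cells | Gives a viability figure for another aliquot | Dead cells are not removed individually from the cytokeratin tube |

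No row delivers what the section describes, namely cytokeratin-positive cells from which the non-viable ones have been gated out.

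**Would the other printed steps catch this?** *Asservation of urine cells* has viability and quantity measured in a cell counter before freezing at -80°C. That describes the sample before freezing and does not remove individual dead cells at staining. The named positive control is for PD-L1; no cytokeratin-positive control is named that would show whether such cells survive the full gating sequence. Because fresh and thawed cells are both allowed, membrane leakiness may differ between samples for reasons unrelated to the kidney.

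**Which readouts are affected?** The total tubular count and the proximal and distal counts within cytokeratin-positive cells. The podocyte readout uses podocalyxin and does not depend on cytokeratin.

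**The case against.** The strongest reply is that this is a condensed article. It defers to standard protocols and to cited work, so permeabilisation, staining order and tube layout may sit in a laboratory procedure that is not shown. It also speaks of antibody mixtures in the plural, and does not say that cytokeratin and propidium iodide are used in the same tube. If the only gap were an unstated permeabilisation step, this reply would succeed.

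It does not succeed here, because adding that step breaks the viability gate that the article names, and a separate aliquot cannot gate out dead cells in the cytokeratin tube. The laboratory procedure may well be sound, but it would have to differ from the printed rule. What stands is that the article alone cannot show what is done at the bench.

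A second reply is that the *Introduction* and *Discussion* report earlier detection of urinary PD-L1+ kidney cells, correlated with intrarenal PD-L1 and with renal adverse events. This weighs against calling the whole assay unworkable. The article does not say how tubular cells were gated in that work, however, and detection alone does not exclude leak-dependent or background staining.

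A reader might infer that tubular PD-L1+ cells cannot be measured at all, or that the tubular gate will be practically empty. The documents do not support that. CD10 and EpCAM can still be read on viable cells, and nothing in the article allows the loss to be sized. A reader might also add that propidium iodide emits close to PE, the podocyte label. That is secondary: detector choice and compensation are not described and may deal with it.

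**Conclusion.** The concern holds in a limited form. The printed tubular definition and the printed viability rule conflict when applied to the same cells, and the reference to standard protocols does not remove the conflict. The tubular PD-L1+ readouts may therefore partly measure membrane damage and sample handling.

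Neither the size nor the direction of the effect can be derived from the documents. The point does not touch the sample size or any error rate; the article states that its comparisons are not formally powered.

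The conclusion rests on two assumptions: the general cell biology given as inputs 5 and 6, and the reading that both gates are meant for the same cells. The second is the natural reading of a rule to gate out non-viable cells, and the five distinct labels are consistent with it. Because the tubular compartment is central to the proposed marker and the correction is cheap, it should be settled before further samples are stained.

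**What to change.** Choose one of two sequences and state it in order.

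1. **Keep cytokeratin.** Replace propidium iodide with a fixable viability dye applied before surface staining. Then stain PD-L1, podocalyxin, CD10 and EpCAM, fix and permeabilise, and stain cytokeratin last. Cost: a reagent change, a little more bench time and some cell loss.
2. **Keep propidium iodide.** Leave the cells unpermeabilised, drop cytokeratin from the tubular gate, and define tubular cells by the surface markers CD10 (proximal) and EpCAM (distal) already in the panel. Cost: less specific tubular identification.

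With either choice, include a cytokeratin-positive control: under the first to show that such cells pass the full sequence, under the second to show how well the surface markers pick out epithelial cells. Record for each sample whether it was stained fresh or after thawing, so that handling can be examined in the analysis. If the laboratory procedure already follows one of these sequences, correcting the printed description is enough. Neither option changes anything for patients.

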### Residual material of renal biopsies

During clinical ICI treatment, the indication for renal biopsies in cases of kidney injury depends on the responsible nephrologist. Residual material of renal biopsies can be utilized for additional diagnostic procedures if ICI-related nephrotoxicity is suspected.

### Immunofluorescence

For immunofluorescent stainings, primary antibodies against PD-L1 (ab205921, Abcam, Cambridge, UK) and Alexa Fluor 488 (Invitrogen, Carlsbad, CA) secondary antibodies will be used, nuclear staining will be performed using 4’,6-diamidino-2-phenylindole (Vector Laboratories).

### Immunohistochemistry

Formalin-fixed, paraffin-embedded kidney sections will be deparaffinized in xylene and rehydrated in ethanol containing distilled water. Tissue sections will be stained using antibodies against PD-L1 (ab205921, Abcam, Cambridge, UK), and labeling is performed using Novolink™ Polymer Detection System (Leica Biosystems, Wetzlar, Germany) according to the manufacturer’s protocol. Nuclear counterstain will be performed using Mayer’s Hematoxylin Solution (Sigma, St. Louis, USA).

### Sample size calculation

Due to the explorative design of the current study evaluating potential parameters that affect the risk of irAEs, the sample size calculation is not hypothesis-driven. Based on the feasibility to enroll, analyze, and follow up, a total number of 200 patients was chosen. The aim of the current study is the hazard ratio assessment of different influencing factors on irAEs related to the kidneys.

### Statistical methods

To assess putative correlations between compiled data, regression methods (Cox regression, logistic regression, Poisson regression) will be performed. Moreover, time-to-event analyses and Kaplan-Meier survival estimates will be conducted. Variables will be tested for normal distribution using the Shapiro-Wilk test. Non-normally distributed continuous variables will be expressed as the median and interquartile range (IQR), and categorical variables as frequency and percentage. Statistical comparisons are not formally powered or prespecified. The Mann-Whitney U-test will be used for group comparisons to determine differences between median values. Spearman correlations will be visualized by heatmaps reflecting mean values of Spearman’s ρ. If not otherwise, specified all calculations are performed with GraphPad Prism (Version 9.5.0 for macOS, GraphPad Software, San Diego, California USA, “www.graphpad.com”) or STATA (STATA/MP version 16.1 for Windows, Stata Corp LLC, College Station, TX, USA). Due to the non-interventional, observational, and prospective study design, hypothesis testing will not be conducted.

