## Introduction

With the advent of immune-checkpoint inhibitors (ICIs), the scope of cancer-treatment options has seen a powerful increment, wherein reactivation of CD8-positive T-cell cytotoxicity constitutes its functional ground (1). Established neutralizing antibodies are directed against co-inhibitory auxiliary proteins expressed on tumor cells engaging in mechanisms of so-called immune evasion. Blockade of programmed cell-death protein 1 (PD-1) and its ligand 1 (PD-L1) is associated with remarkable therapy responses, especially for solid tumor entities featuring restricted therapeutic options. Still, immune-related adverse events (irAEs) pose a serious threat to treatment success, including maintenance of tumor remission (2–6). Of these irAEs, skin, gastrointestinal, hepatic, and endocrine adverse effects are the most common (7). Kidney involvement is known to occur with an incidence ranging from 2 to 3%; subclinical affection is estimated even higher, up to 29% (8–16). Glucocorticoid therapy and discontinuation of the causative agent are the only available measures with the side effect of delayed cancer treatment. Once affected, kidneys are more prone to a renal relapse after ICI re-exposition (9–11). Nephrotoxicity related to ICI therapy mainly consists of acute interstitial nephritis (AIN) and, to a lesser extent, glomerular nephropathies (8–19). This nephrotoxicity remains unclear and deserves to be characterized regarding clinical patterns and the underlying mechanisms.

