## Methods

### Study design and study population

Our observational single-center study is prospective, controlled, longitudinal, and non-interventional (trial registration: https://www.drks.de, DRKS-ID: DRKS00030999). It will be performed at the Department of Nephrology and Rheumatology at University Medical Center Göttingen (UMG), Germany. In addition, cancer patients receiving ICI treatment at the Departments of Dermatology, Urology, Hematology, and Medical Oncology of the UMG will be enrolled. The type and dosing schedule of the ICI therapy will be performed as indicated by the responsible medical specialist and carried out independently from the study investigations. A sample size of 200 patients was calculated based on the reported incidences of ICI-related nephrotoxicity.

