### Patient enrollment and study conduction

Inclusion criteria are patients 18 years or older, written informed consent, and intended immunotherapy. In addition, patients enrolled in other ongoing trials of immunotherapies with a blinded study design are considered ineligible. Within the framework of routine medical care of patients in the respective departments, eligible patients are identified and included after documented written consent. **Figure 1** shows a STROBE flow chart of the study protocol featuring an overview of inclusion and exclusion criteria. After providing written consent, a baseline visit will be conducted, where baseline demographic data, medical history, medication, and clinical symptoms will be collected. Physical examination includes the assessment of height, weight, vital parameters, general condition, the status of the integument, neck with the thyroid gland, head, ears, eyes, throat, abdomen, limbs, joints, and auscultation of the heart and lungs. Laboratory data assessments include differential blood cell counts, serum levels of sodium, potassium, calcium, creatinine, blood urea nitrogen (BUN), uric acid, aspartate aminotransferase (AST), alanine aminotransferase (ALT), gamma-glutamyl transferase, bilirubin, lactate dehydrogenase (LDH), lipase, blood glucose, creatine kinase (CK), thyroid-stimulating hormone (TSH), T3, T4, and CRP. In addition, viral serology for the human immunodeficiency virus (HIV), hepatitis A, B, and C, cytomegalovirus (CMV), and the Epstein-Barr virus (EBV) will be tested at baseline. Moreover, autoantibody testing will be performed once at baseline and afterward as clinically indicated and includes antinuclear antibodies (ANA), anti-neutrophilic cytoplasmic antibodies (ANCA), extractable nuclear antigen (ENA), anti-double stranded desoxyribonucleic acid (anti-dsDNA), anti-cyclic citrullinated peptide (anti-CCP) and rheumatoid factor (RF). In addition, urinanalysis will be performed at each visit with urine dipstick and urine sediment, and an additional asservation of 100 mL of fresh urine samples will be performed. Follow-up visits are scheduled every 12 (–16) weeks; unscheduled visits will be performed if an irAE is suspected. The end-of-study visit will be conducted after 48-52 weeks. The schedule of visits and assessments is shown in **Table 1**.

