## Discussion

Kidney affection occurring as an irAE during immunotherapy is a severe and potentially life-threatening complication endangering treatment success, hence the overall survival of cancer patients. Clinically apparent renal involvement is estimated to occur with an incidence of 3%. In contrast, previous investigations of biopsy-proven ICI-related nephrotoxicity reported a much higher frequency of up to 29% of cases implying that conventional diagnostic methods only detect advanced and pronounced kidney injury and are unable to detect early and milder forms of renal involvement (8–16). Renal biopsy is the gold standard for the etiological assignment of kidney affection but carries an increased risk of bleeding complications in the cancer-patient population. Moreover, repeated renal biopsies during a complete treatment course iteratively subject patients to the risk of hemorrhagic events. Despite discontinuing ICI treatment and steroid therapy, the kidneys stay endangered to relapse. In case of renal relapses due to cancer-treatment continuation, the clinical course may even be more fulminant, requiring kidney replacement therapy (KRT) (2). Thus, new tools for biomonitoring in clinical routine will be helpful for the early detection of complications.

Our study aims to evaluate the urinary detection of PD-L1^+^ kidney cells based on urinary flow cytometry as a non-invasive biomonitoring tool for renal complications in cancer patients treated with immunotherapy. The concept of urinary flow cytometry-based detection of renal and immune cells reflecting so-called “biosignatures” was first described for renal allograft pathology (22, 23). Adapted from receiver operating characteristics-(ROC)-curve analyses, an assignment of urinary detected cellular components and renal allograft rejection, including T-cell mediated rejection (TCMR), was enabled (22). The conceptual extension of these findings to other T-cell-mediated renal pathologies, for example, ICI-related nephrotoxicity, seems attractive. Moreover, we previously reported intrarenal PD-L1-positivity as a potential indicator of ongoing kidney damage, showing that renal irAEs correlate with detected PD-L1^+^ kidney cells in the urine (20, 21). PD-L1 upregulation was also observed in other renal pathologies implying PD-L1 functions as a response signal to injuries within the kidneys (20).

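### At the article's 2–3% clinical incidence, ordinary Cox, logistic and Poisson fits often give no finite ratio for yes/no factors, and biased finite ratios for uncommon ones

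*Protocol article*

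**What the plan says.** The Sample size calculation section states the goal: "The aim of the current study is the hazard ratio assessment of different influencing factors on irAEs related to the kidneys". It adds that "a total number of 200 patients was chosen" on grounds of feasibility. For estimation, the Statistical methods section says that "regression methods (Cox regression, logistic regression, Poisson regression) will be performed", using GraphPad Prism or STATA unless specified otherwise. It names no penalised, bias-reduced or exact variant. It also says that comparisons are neither powered nor fixed in advance, and that no hypotheses will be tested.

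On event frequency, the Introduction says "Kidney involvement is known to occur with an incidence ranging from 2 to 3" per cent, and the Discussion says "Clinically apparent renal involvement is estimated to occur with an incidence of 3" per cent. Both also mention milder or subclinical involvement at up to 29%. The article does not say which rate belongs to its endpoint.

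Candidate factors are not listed. The baseline data do include several items that are naturally yes/no. Viral serologies are one group. Autoantibodies are another: "autoantibody testing will be performed once at baseline and afterward as clinically indicated".

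**The concern.** Standard Cox, logistic and Poisson regression are fitted by maximum likelihood. For a yes/no factor, the likelihood has a finite maximum only if at least one event falls on each side of the factor. With a handful of events this often fails: the ratio runs to zero or infinity, or the software drops the variable. Nothing more than one factor at a time is needed, so this is a question about the estimator and not about the choice of 200.

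The finite ratios are then a selected set. For an uncommon factor, a finite value requires that an event happened to fall in a small group, which pushes the ratio up. Since no hypotheses are to be tested, the ratios are the main product. Uncommon factors with no effect could look like strong risk factors, and others could vanish from the results because no ratio could be computed.

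**Working it through.** **Inputs from the article.** N = 200; clinical incidence 2–3%; alternative rate up to 29%. There is no alpha, power, effect size or precision target behind the 200, so there is no planned figure to reproduce.

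**Assumptions.** Factor prevalences (10, 20, 30, 50%) and true ratios are mine, because the article gives none.

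**Step 1, events.** Expected events = 200 × incidence: 200 × 0.02 = 4; 200 × 0.03 = 6; 200 × 0.29 = 58. Under a binomial model the central 95% range is 1–8 at 2% and 2–11 at 3%. The chance of fewer than 10 events is 99% and 92%.

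**Step 2, no finite ratio, fixed event count.** For a null factor of prevalence q, the chance that all E events fall on one side is (1 − q)^E + q^E.
- q = 10%: 0.9^4 + 0.1^4 = 66%; 0.9^6 + 0.1^6 = 53%
- q = 20%: 0.8^4 + 0.2^4 = 41%; 0.8^6 + 0.2^6 = 26%
- q = 30%: 25% (4 events); 12% (6 events)
- q = 10% with 58 events: 0.2%

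**Step 3, random event count.** The logistic 2×2 estimate was enumerated exactly over Binomial(200q, p1) × Binomial(200(1 − q), p0), with overall incidence held fixed. GM is the geometric mean; each cell gives 2% / 3% incidence.

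| Prevalence, true OR | No finite OR | GM of finite ORs |
|---|---|---|
| 10%, OR 1 | 68% / 55% | 3.32 / 2.34 |
| 20%, OR 1 | 47% / 30% | 1.85 / 1.42 |
| 30%, OR 1 | 34% / 17% | 1.39 / 1.16 |
| 50%, OR 1 | 25% / 9% | 1.00 / 1.00 |
| 30%, OR 3 | 25% / 10% | 2.78 / 2.93 |
| 30%, OR 5 | 32% / 15% | 3.82 / 4.48 |
| 50%, OR 3 | 39% / 22% | 1.94 / 2.41 |

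**Why the null 10% factor is pushed up.** There are 20 exposed and 180 unexposed patients, and the smallest usable count is one exposed event. With 4 events the OR is (1/19)/(3/177) = 3.11; with 6 it is (1/19)/(5/175) = 1.84. It falls to 1 only with 10 events in total: (1/19)/(9/171) = 1. Fewer than 10 events are nearly certain, so 99% (2%) and 93% (3%) of finite estimates lie above the truth.

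**Step 4, Cox.** Simulation of the partial likelihood (1,500 runs per setting) agrees. A null 10% factor had no finite HR in 66% / 55% of runs, and finite HRs averaged 3.2 / 2.4. At 50% prevalence and true HR 3 they averaged 1.97 / 2.42. One standardised continuous marker was estimable in about 98% or more of runs, with HR 2 estimated as 2.11–2.12.

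**Step 5, the 29% rate.** A null 10% factor has no finite OR in about 0.1% of samples, and finite ORs average 0.95.

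**Step 6, Firth.** For a single yes/no factor, Firth's logistic fit equals adding 0.5 to each cell, so it is always finite. Over all samples the null 10% factor averages 1.82 (2%) and 1.44 (3%); the null 20% factor averages 1.27 and 1.12. At 3% incidence, 10% prevalence and true OR 3, it averages 3.20.

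**The case against.** **The article is condensed.** It names model families, not maximum likelihood, and an unseen full plan could specify a penalised fit. That is a fair limit on confidence. But the article does fix the methods and default software for its stated aim, and nothing in it points to a small-event variant.

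**Factors and rate are not fixed.** No serology or autoantibody is named as a covariate, and the leading marker may well enter as a continuous variable, where the problem is small. This stands, and the prevalences above remain assumptions. The 29% rate would also remove the problem. However, the Discussion ties that rate to biopsy-proven disease, biopsy is done only when the nephrologist sees an indication, and the visit schedule contains none. Clinically apparent cases at 2–3% are therefore the likelier endpoint.

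**The study is exploratory.** This lowers the consequence but does not remove it, because the hazard ratios are the declared aim.

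**Stronger readings that do not hold.** A reader might infer that every finite ratio is inflated. It is not. At 50% prevalence and true OR 3 the finite ratios average 1.94–2.41, which is too low; at 3% incidence, 30% prevalence and true OR 3 they average 2.93, nearly unbiased. A reader might also infer that Firth works by shrinking each estimate towards 1. For a null 10% factor at 2% incidence, in samples where both estimates exist, Firth's averages 3.99 against 3.32. Its benefit is a finite, less biased estimate over all samples.

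**Conclusion.** The point holds for yes/no factors at the 2–3% endpoint. With 4–6 expected events, a null factor has no finite maximum-likelihood ratio in 55–68% of samples at 10% prevalence and in 30–47% at 20%. Finite ratios are biased upward for uncommon factors (average OR 2.3–3.3 for a null 10% factor) and can be too low for common factors with strong effects.

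This rests on three things: that kidney irAEs occur at the clinical rate, that uncommon yes/no factors are modelled, and that the named regressions are fitted in their ordinary form. It does not extend to a single continuous marker to any important degree, nor to an endpoint at 29%. The wording should be changed, because a better method is available at little cost and does no harm if the event count proves higher.

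**What to change.** In Statistical methods, state that:
- Cox and logistic models for kidney irAEs use Firth's penalised likelihood with profile penalised-likelihood 95% intervals, and any Poisson model uses the matching bias-reduced fit;
- every examined factor is reported with event counts per category, including those with no event in one category;
- PD-L1+ cell readings stay continuous in these models.

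The cost is a few lines of text and an add-on routine, which the section's allowance for other specifications permits. No new patients or data are needed. The limits should be stated too: intervals will remain very wide, because Firth does not cure the imprecision of 4–6 events, and some upward bias persists for rare factors (average OR about 1.4–1.8 for a null 10% factor).

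### If Kaplan-Meier is used for kidney irAE with deaths censored, it overstates the one-year risk; report cumulative incidence with death as a competing event

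*Protocol article*

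**What the plan says.** The Statistical methods section of the protocol article states that "regression methods (Cox regression, logistic regression, Poisson regression) will be performed", and continues: "Moreover, time-to-event analyses and Kaplan-Meier survival estimates will be conducted". It does not say which endpoint the Kaplan-Meier estimates describe, or how a patient who dies before a renal event enters any of these analyses.

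The target event has to be read from elsewhere. The section on sample size says: "The aim of the current study is the hazard ratio assessment of different influencing factors on irAEs related to the kidneys". The abstract's methods paragraph plans to relate urinary PD-L1-positive cells to the onset of ICI-related nephrotoxicity. Overall survival appears only as motivation, in the abstract's discussion paragraph and in the Discussion; no section makes it a study outcome.

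On follow-up, the section on enrollment and conduct says: "The end-of-study visit will be conducted after 48-52 weeks". On event rates, the Introduction says: "Kidney involvement is known to occur with an incidence ranging from 2 to 3%; subclinical affection is estimated even higher, up to 29" per cent. The study is exploratory, with 200 patients and no hypothesis testing.

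**The concern.** A cancer patient who dies at week 20 without a renal irAE can no longer have one. Kaplan-Meier with that death censored treats the patient as still able to have the event later. Its complement is then the risk in a hypothetical setting without death, which is at or above the proportion of patients in whom a renal irAE is actually seen.

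Two outputs are at stake: the overall one-year incidence of renal irAE, and the curves by urinary PD-L1 status if they are read as absolute risks. In an exploratory study without formal tests, descriptive estimates of this kind are a main product, and a tool for monitoring patients is judged on actual risk. The error also does not shrink as the sample grows.

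**Working it through.** **No figure to reproduce.** The article states no cumulative incidence, mortality, power or event count, so the check is of direction and size only.

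**Inputs from the article.** N = 200; follow-up of about one year; renal event rate 3% (clinical) or up to 29% (subclinical).

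**Assumptions.** Mortality within the year is not given, so it is varied. Both hazards are taken as constant.

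**Step 1: size of the overstatement.** Let C be the true one-year probability of a renal irAE and D the probability of dying first without one.
- Total hazard: L = -ln(1 - C - D).
- Renal hazard: h = L × C / (C + D).
- Kaplan-Meier with deaths censored gives 1 - exp(-h).

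| C | D | L | h | 1-KM | Excess (points) |
|---|---|---|---|---|---|
| 3% | 20% | -ln 0.77 = 0.2614 | × 3/23 = 0.0341 | 3.35% | 0.35 |
| 3% | 35% | -ln 0.62 = 0.4780 | × 3/38 = 0.0377 | 3.70% | 0.70 |
| 3% | 50% | -ln 0.47 = 0.7550 | × 3/53 = 0.0427 | 4.18% | 1.18 |
| 29% | 20% | -ln 0.51 = 0.6733 | × 29/49 = 0.3985 | 32.9% | 3.9 |
| 29% | 35% | -ln 0.36 = 1.0217 | × 29/64 = 0.4629 | 37.1% | 8.1 |

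**Step 2: sensitivity to the definition of mortality.** Define mortality instead as the death probability in the absence of a renal event, and solve C = h/(h + m) × (1 - exp(-(h + m))) for h, with m the death hazard. For mortality of 10, 20, 30 and 50%:
- a true 3% reads as 3.16, 3.35, 3.56 and 4.15%;
- a true 29% reads as 30.5, 32.1, 34.1 and 39.1%.

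The direction is the same and the size similar.

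**Step 3: comparison with sampling error.** The 95% half-width is 1.96 × sqrt(p(1 - p)/200).
- At 3% (200 × 0.03 = 6 events) it is 2.4 points, larger than every excess above.
- At 29% (58 events) it is 6.3 points. The excess is below this at 20% mortality and approaches or passes it from about 35%.

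**Step 4: effect on the Cox hazard ratio.** Data were simulated with a true renal hazard ratio of 2 and 2 million patients per scenario. With deaths censored, the estimated hazard ratio was 1.99 to 2.01, both with equal mortality (20% in each group) and with 20% versus 50%.

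**Step 5: logistic regression.** In the same simulation, with 20% mortality in both groups and deaths counted as non-events, the crude one-year risks were 2.7% and 5.3%. One minus Kaplan-Meier gave 3.0% and 5.9%. The crude risk is the actual risk, the same quantity that a cumulative incidence function estimates. The odds ratio does depend on mortality: it was 2.04 with equal mortality and 1.62 with 20% versus 50%, although the renal hazard ratio was 2 in both.

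**The case against.** The strongest objection is that the Kaplan-Meier sentence names no endpoint. It speaks of survival estimates, and the article mentions overall survival elsewhere. If overall survival was meant, Kaplan-Meier is the right method. A condensed article may also leave the handling of deaths to a fuller document that is not shown. This stands in part: the renal endpoint is an inference, and silence about deaths is not in itself a fault. But the renal irAE is the only event the article sets as a target and Kaplan-Meier is the only time-to-event summary it names, so the inference is the natural one.

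A second objection is that the aim is hazard ratios, not incidence. This stands fully for the Cox analysis, as Step 4 shows.

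A third is that the size is assumed and often small. This also stands. No mortality is given, and at 3% the excess is lost in the sampling error. The 29% case is uncertain as a rate this study would observe: the Introduction calls it subclinical, the Discussion ties it to biopsy-proven disease, and biopsy is left to the responsible nephrologist.

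A reader might also infer more than the article supports:
- That logistic regression makes the opposite error by counting deaths as non-events. It does not; that coding gives the actual crude risk (Step 5). Trouble arises only if patients who leave alive are coded as full-year non-events, and the article does not say they are.
- That differing mortality distorts the comparison of PD-L1 groups. As a contrast of cause-specific hazards it does not; only reading the curves as absolute risks fails. The article links PD-L1 to CRP, not to mortality.
- That the Poisson model lacks a person-time offset, or that follow-up stops when ICI treatment stops. The article says neither.

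**Conclusion.** The point holds as a conditional one. If Kaplan-Meier is used for renal irAE with deaths censored, its complement overstates actual one-year risk. The excess is about 0.4 to 1.2 points at a true 3% for assumed mortality of 20 to 50%, and about 4 to 8 points at a true 29% for assumed mortality of 20 to 35%. The first is within sampling error; the second can exceed it. These sizes rest on assumed mortality, constant hazards and an inferred endpoint.

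The documents do not support the stronger conclusion that the study's stated aim is compromised. Cox regression with deaths censored gives a valid cause-specific hazard ratio. This is an inexpensive improvement to the descriptive analysis and does not call the design into question.

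**What to change.** In the Statistical methods section:
- Name the endpoint of the Kaplan-Meier estimates and keep them for overall survival only.
- For renal irAE, overall and by PD-L1 status, report Aalen-Johansen cumulative incidence with death as a competing event.
- Label the Cox estimates as cause-specific hazard ratios and add a companion cause-specific model for death.
- Treat any logistic model of one-year renal irAE as secondary and read it as a model of crude risk. Do not code patients who leave alive before 48 weeks as full-year non-events.
- Record date of death, which the visit schedule in Table 1 does not list.

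The cost is a few sentences, slightly more analysis work and one data field. The methods are available in the software the article names. Enrollment and visits do not change.
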